### Outcomes

Outcome data are collected through the use of (1) direct child assessments with eye tracking (Tobii X3-120, Tobii technology, Stockholm), Electroencephalography system (EEG; 128 channel net, Electrical Geodesics Inc., EGI), video-recorded observations, and a tablet test, (2) video-recorded structured observations of parent-child interaction, and (3) parental questionnaires. Study outcomes are presented in Table 2.

**Table 2 Tab2:** Study outcomes and measures

Outcomes	Measures	Method	Baseline assessment (T1)	Intervention	Post-assessment (T2)	First follow-up (T3)	Second follow-up (T4)
***Primary outcomes***							
Child language	Receptive	Eye tracking: *preferential looking task*	x		x	x	
		Eye racking: *pupil dilation task*	x		x		
		EEG: *N400*	x		x		
		Parent report: *CDI*	x		x	x	x
	Expressive	Parent report: *CDI*	x		x	x	x
Child socio-cognition (joint attention)	Initiating joint attention	Observation: *ESCS*	x		x	x	
	Responding to joint attention	Observation: *ESCS*	x		x	x	
***Secondary outcomes***							
Child executive function		Parent report: *EEFQ*	x		x	x	x
	Simple inhibition	Observation: *“prohibition task”*				x	
	Inhibitory control	Tablet task: *ECITT*				x	
	Working memory	Observation: *“hide and seek task”*				x	
	Shifting	Observation: *reversed categorization*				x	
Parental behavior	Sensitivity and reciprocity	Observation: *BSSI*	x		x		
	Cognitive scaffolding	Observation: *BSSI*	x		x		
	Cognitive scaffolding	Observation: *“problem solving task”*	x		x		
***Moderators***							
Parental socio-economic status	Parental level of education	Parent report	x				
Home literacy environment	Reading habits	Parent report	x		x	x	x
Parental intervention compliance	Attendance record, intervention dose (amount of practice), intervention experience	Facilitator/parent report		x			

*Abbreviations*: *EEG* Electroencephalography, *CDI* Communication Development Inventory, *ESCS* Early Social Communication Scale, *EEFQ* Early Executive Functions Questionnaire, *ECITT* the Early Childhood Inhibitory Touchscreen Task, *BSSI* the Book Sharing Scale for Infants

### Primary outcome measures

#### Child language

Parental reports on a short-version of the *Swedish Early Communication Development Inventory* (CDI) [41] are used at all assessments for assessing *word production and word comprehension* (i.e., expressive and receptive language). From this 90-item checklist, we calculate aggregated scores for expressive and receptive language and used as outcome variables.

*An eye tracking word-picture matching paradigm* is used for assessing *word comprehension* (i.e., *receptive language*) based on the child’s preferential looking pattern [42, 43] at baseline, post-assessment, and first follow-up. This is a screen-based assessment that comprises 32 test trials (i.e., paired-picture trials). All pictures consist of color images of objects representing common nouns (e.g., mouth, bottle, foot). The pictures are presented on a 22″ screen and the participant’s gaze is recorded at 60 Hz with a Tobii X3-60 eye tracking camera (Tobii Technology AB, Stockholm, Sweden). On each test trial, the participant is presented with a pair of pictures for 2500 ms, while hearing a prerecorded sentence that directed them to look at one of the pictures (object/noun). For each trial, we calculate the participants dwell time to the target object (picture) and the distractor object (picture) during an analysis window of 367–2500 ms. We then calculate the proportion of target looking time by subtracting the time the child looked at a picture when it was a distractor from the time when it was a target. Proportion of target looking time was averaged across trials and used as the outcome measure.

*An EEG and eye tracking based mismatch-paradigm* [44] is used to assess child *word comprehension* at baseline and post-assessment. The child participants sit in front of 22″ monitor, with a Tobii X3-60 eye tracker attached to its bottom, while wearing a 128-channel Geodesics Sensor Nets. This task consists of 48 trials. Every trial starts out with displaying a scene consisting of a floor and a blue occluder on the monitor. A sentence with a word (“Look at X”) was presented over headphones to the caregiver who has been instructed to repeat the sentence to their child. Once the sentence is uttered, the experimenter pushes a button. Following this, the occluder disappear and an object (representing a common noun, e.g., a duck, a ball, or a car) is revealed. Objects are congruent (50%) or incongruent (50%) with the word spoken by the caregiver. This task has two outcome measures: (1) we measured an event-related brain potential known as the N400 (based on differential amplitude on congruent and incongruent trials, averaged across trials), and (2) we measure a pupil dilation difference score based on differential dilation on congruent and incongruent trials, baseline corrected and averaged across trials (see for example [45]). For both measures, the assumption is that if the child has developed a word knowledge of a specific word/object, they will detect the mismatch between presented word and object on incongruent trials. This mismatch is then reflected in enhanced N400 amplitude and increased pupil dilation on incongruent trials (vs congruent trials).

#### Child joint attention

The child’s ability to *initiate and respond to social communication*, that is, *joint attention skills*, is assessed with two tasks, the *Object Spectacle* Task and the *Gaze Following Task*, from the Early Social Communication Scales (ESCS) [46]. This assessment is made at the baseline, post-assessment and at the first follow-up assessment. In both tasks, the experimenter and the child are sitting at a table facing each other.

In the *Object Spectacle* Task, the experimenter activates a toy for 6 s in front of the child, but out of the child’s reach. This procedure is repeated for a total of 9 trials using three different toys (a wagging dog, a hand puppet, and a rattle). In each trial, we measure the child’s number of alternating gazes between the toy and the experimenter based on video records. The outcome measure is the proportion of alternating gazes across trials.

The *Gaze Following Task* involves a sequence of the experimenter pointing and gazing at four posters hanging on the wall. The four posters are located to the left, right, left behind, and right behind the child. The child is presented with a total of 8 trials (i.e., every poster is the target on two occasions). On all trials, the experimenter captures the child’s attention and then turns to point and gaze toward a poster. Based on video records, we calculate the proportion of correct responses (i.e., gaze following) and use this as our outcome measure.

### Secondary outcome measure

#### Child executive function

Child EF is assessed at all four assessments using the Early Executive Functions Questionnaire (EEFQ) [47]. This is a 31-item questionnaire (using a 7-point scale) consisting of four sub-scales: *Inhibitory Control*, *Working Memory*, *Flexibility*, and *Regulation*. We will use the mean scores from this questionnaire as outcome measures.

Child EF is also assessed at the first follow-up assessment with four different observational lab tasks targeting *simple inhibition*, *inhibitory control*, *working memory* and *shifting (or cognitive flexibility)*. *Simple inhibition* is measured by the “Prohibition Task” [48]. The child and the experimenter sit at a table facing each other. The experimenter presents an attractive toy to the child. While having eye contact with the child, the experimenter shakes their head and says: “now, (“child’s name”), you are *not* allowed to touch this” while simultaneously placing the toy on the table within the child’s reach. The outcome variable is the latency to touching the toy, with a maximum of 30 s, and will be coded from video records. A longer waiting time indicates higher inhibition.

*Inhibitory control* was assessed with the Early Childhood Inhibitory Touchscreen Task (ECITT) [49]. During this task, the child sits next to the parent. The experimenter holds an iPad in front of the child. Following a warm-up game to get familiarized with the tablet and one warm-up trial, two buttons, one at the left and one at the right, are presented on the screen and the child is instructed to press the button with the happy face. If the child presses the correct button, an animation is shown. If the child presses the incorrect button, no animation is shown. The happy face appears in the same (prepotent) location on 24 trials (75% of trials) and in the inhibitory location on 8 trials (25% of trials). The outcome measures are reaction time (i.e., time between presentation of the buttons and the child’s button pressing) and mean accuracy (i.e., percentage correct in prepotent trials minus the percentage correct in inhibitory trials). A larger score indicates lower inhibitory control.

*Working memory* is assessed with a hide-and-seek task [50]. The hiding locations are colored drawers, part of a small table chest. The tasks consist of two warm-up trials and four test trials. The child and the experimenter are sitting at a table. On each trial, the experimenter hides the toy in one of the drawers while saying “Now I am hiding it here” and then covers the chest with a cloth. After 5 s, the child is encouraged to search for the toy. The child receives a score of 4, 3, 2, or 1 according to whether they were successful on the first, second, third, or fourth attempt, respectively. Children who did not succeed after four attempts are given a score of 0. The mean score over all test trials was calculated and used as the outcome measure. This score was coded from video records. A larger score indicates stronger working memory.

*Shifting* is assessed with the task Reversed Categorization [51]. The child and experimenter were sitting at a table. Children are asked to sort red and yellow blocks into a red and yellow bucket according to their color and then to reverse this categorization so that yellow blocks would go to the red bucket and vice versa. We calculate proportion of correctly sorted blocks on the categorization trials (according to color; raw score = 0–6) and the reversed trials (raw score = 0–12). The outcome measures were coded from video records. A larger score indicates stronger shifting abilities.

#### Parental scaffolding, sensitivity, and reciprocity

Parental cognitive scaffolding, sensitivity and reciprocity are being assessed by structured observations of parent-child interactions in a book sharing and a problem-solving task. The observations will be coded from video records using the Book Sharing Scale for Infants (BSSI) [52] for the book sharing task, whereas the coding of the problem-solving task is based on the Autonomy Support Scale [53].

### Potential moderators

The following variables will be used as potential moderators: *family socio-economic status* (indexed at baseline by parental report on highest parental education level: elementary school, high school, university < 3 years, or university >3 years ), *home literacy environment* (indexed by parental report on reading habits at all four assessments, e.g., frequency of reading for the child: never, 1–2 times per month, 1–2 times per week, or everyday/almost every day), and *parental intervention compliance* (indexed by intervention sessions attendance records, and self-reported practice of shared-reading between session, reported as days per week and minutes per day, and intervention experience, e.g., whether they think the book sharing training has been beneficial to them).

### Other measures

The study will also include questionnaire items on demographic information. For example, information on parental age and gender, first language, child monolingualism status, and gender. The participants will additionally be assessed with the Bayley Cognitive and Fine Motor Skills Scale (Bayley Scales of Infant and Toddler Development-III] [54]. This data will be used for descriptive purposes and for examining whether demographic characteristics and the Bayley-III outcome measures are balanced between the index and control group at baseline.

### Sample size

The originally targeted sample size was 140 children (10-month-old ± 4 weeks) and their caregivers (70 dyads in each arm). The sample size was calculated on the basis of the primary outcome measure language. The power calculation was conducted in G*Power [55] using 80% power and alpha set to = .05. The effect size (*d*) for the power calculation was based on the results reported in a recent meta-analysis by Dowdall et al. [26]. The meta-analysis [26] was based on RCT book sharing interventions targeting young children (1 to 6 years) and reported an overall effect size of *d* = .54 for expressive language in studies using medium to high intensity intervention dose (i.e., more than 60 min contact time). Based on this estimate, an index and control sample of 55 dyads in each arm would therefore be sufficient to detect a difference (two-tailed) and would allow for an attrition rate > 10%. The study’s final sample size was 115 parent-child dyads (index group, *n* = 59; active control group, *n* = 56). Thus, the study’s sample size is sufficiently powered.

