Two recent meta-analysis [26, 28] have assessed the effect of parental interactive book sharing on 1- to 6-year-old children’s language gain in randomized controlled studies (RCT) studies. Both studies corroborate the conclusion of the efficacy of interactive book sharing for children’s vocabulary development. The study by Dowdall et al. [26] reported small sized effects on expressive (*d* = .41, CI = .20, .61) and receptive (*d* = .26, CI = .12, .40) vocabulary, but larger effects were found for studies with medium to high intervention dose (i.e., more than 60 min contact time). This meta-analysis also showed a large sized intervention effects on caregiver book sharing competence (*d* = 1.01, CI = .40, 1.63), such as “caregiver expansion during book sharing,” “parental sensitivity and reciprocity during book sharing,” and “caregiver use of an interactive reading style.” However, one important caveat is that only five of the 19 studies included in the meta-analysis provided such data and these studies were limited due to small sample sizes and/or absence of an active control group. It was further reported that group-based interventions were associated with greater intervention gains in language compared to one-on-one interventions. Although speculative, the latter finding could indicate that the group-based format offered more learning opportunities through participant sharing their experiences or through increased social support [26]. Another possibility is that the group format increased participant adherence to the intervention protocol. This finding also points to the importance of using an adequately designed active control group instead of a no-contact (wait-list) group to control for nonspecific intervention effects, such as effects of increased social support in group interventions.

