### Recruitment

Recruitment began in January 2020 and ended in August 2021.^3^ The first recruitment wave took place in January to February 2020, the second recruitment wave took place between May and October 2020, and the third recruitment wave took place between July and August 2021. Participants were recruited to the study using several methods. A part of the sample was recruited from the BASIC project—a large epidemiology study investigating maternal health during and after pregnancy [56]. Mothers participating in the BASIC-project was asked if they were interested in being contacted by the Uppsala Child and Baby Lab about a study on child development. Recruitment also took place by contacting families with a general interest in participating in child developmental studies at the Uppsala Child and Baby Lab. Other means of recruiting potential participants included sending letters describing the study to families in Uppsala municipality, using advertisement for the study on Facebook, and by putting up flyers and verbally informing parents visiting “open pre-schools” in Uppsala. All potential participants, i.e., caregivers with a child of appropriate age who expressed interest in participating in the study, were provided with an invitational package that described the study and included copies of the consent form. Caregivers who expressed an interest in the study were then screened via telephone for eligibility.

Of 187 dyads assessed for eligibility, 151 met all inclusion criteria and none of the exclusion criteria and gave consent to participate in the study. They were then randomized to an index group or active control group. Of these, 115 completed the baseline assessment, 109 completed the post-assessment, and 98 completed the first follow-up assessment at 18 months. The follow-up assessment at 24 months is still ongoing at the current date.

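### The attrition allowance of more than 10% is attached to 55 dyads per arm, which is a bare completer count, and the adequacy claim for 115 dyads is supported only for expressive language at d = 0.54

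*Protocol article*

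**What the plan says.** All of the sizing statements are in the protocol article's Sample size section. It opens with the first target: "The originally targeted sample size was 140 children (10-month-old ± 4 weeks) and their caregivers (70 dyads in each arm"). It then gives the method, "The power calculation was conducted in G*Power [55] using 80% power and alpha set to = .05", and the effect size: the meta-analysis "reported an overall effect size of *d* = .54 for expressive language in studies using medium to high intensity intervention dose". From this it concludes that "an index and control sample of 55 dyads in each arm would therefore be sufficient", and the sentence goes on to say that this number "would therefore be sufficient to detect a difference (two-tailed) and would allow for an attrition rate > 10" per cent. After giving the final sample of 115 (59 index, 56 control), the section ends by saying that the "sample size is sufficiently powered".

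Three other places bear on this:

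- **Recruitment** reports that, of the 115 with a baseline assessment, "109 completed the post-assessment, and 98 completed the first follow-up assessment at 18 months".
- **Background**, on the same meta-analysis, says that it "reported small sized effects on expressive (*d* = .41, CI = .20, .61) and receptive (*d* = .26, CI = .12, .40) vocabulary". The sentence then adds that effects were larger in studies with a medium to high dose.
- **Table 2** lists five child-language measures as primary. Four are receptive (preferential looking, pupil dilation, N400, CDI receptive) and one is expressive (CDI expressive). Joint attention is the other primary outcome.

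**The concern.** A sample size either includes an attrition allowance or is the number that must remain after attrition. The text treats 55 per arm as both, and the conclusion about 115 dyads follows directly from that sentence. A reader would take it that 115 dyads can lose more than a tenth and keep 80% power.

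The second issue is scope. The section says that the sample was sized on language as the primary outcome, but the effect used is for expressive language only, and from the higher-dose studies. Most of the primary language measures are receptive, and the receptive effect quoted in the Background is about half as large. If the claim is read as covering language as a whole, a non-significant receptive result could be taken as a negative finding from an adequately powered trial.

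**Working it through.** **Inputs.** From Sample size: d = 0.54, two-sided alpha 0.05, 80% power, 55 per arm, original target 140, final sample 59 + 56. From Recruitment: 109 and 98 assessed. From Background: expressive d = 0.41 and receptive d = 0.26 (CI 0.12 to 0.40), both over all doses. From Statistical methods: mixed model or analysis of covariance with the baseline score as covariate; no baseline correlation is given.

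**Method.** Two-sample t test with the noncentral t distribution, df = n1 + n2 − 2, noncentrality = d × √(n1·n2/(n1 + n2)).

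**1. The plan's own figure.** At d = 0.54 and 55 per arm, the noncentrality is 0.54 × √(55 × 55/110) = 2.83, df = 108, critical t = 1.98, and power is 80.1%. With 54 per arm it is 79.4%. So 55 per arm reproduces, as the number analysed. A 10% loss from 55 leaves 49.5 per arm and 75.8% power.

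**2. Where an allowance of more than 10% holds.**
- From 140: 1 − 110/140 = 21.4%. It holds.
- From 115: 1 − 110/115 = 4.3%. It does not hold.
- Loss at post-assessment: 6/115 = 5.2%. Loss at 18 months: 17/115 = 14.8%.

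**3. Expressive language at d = 0.54.** The article gives totals only at follow-up, so near-even splits are assumed (56/53 and 50/48).

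| Dyads analysed | Unadjusted power | Detectable d at 80% power |
|---|---|---|
| 115 (59/56) | 81.9% | 0.53 |
| 109 | 79.7% | 0.54 |
| 98 | 75.3% to 75.4% | 0.57 |

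Adjusting for a baseline score with correlation r divides the residual standard deviation by 1/√(1 − r²), so the effective effect is d/√(1 − r²). With r assumed to be 0.5 to 0.7, power at 0.54 is about 90% to 97% with 109 dyads and 86% to 96% with 98.

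**4. Receptive language with 109 dyads.** No receptive effect matched on dose is given. Two values are added as assumptions: 0.26 × 0.54/0.41 = 0.34, which scales the receptive effect by the expressive dose ratio, and 0.40, the upper confidence limit.

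| Receptive d | Unadjusted | r = 0.5 (assumed) | r = 0.7 (assumed) |
|---|---|---|---|
| 0.26 (cited, all doses) | 27% | 34% | 47% |
| 0.34 (assumed scaling) | 42% to 43% | 53% | 69% to 70% |
| 0.40 (upper limit) | 54% | 67% | 83% |

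Without adjustment, 80% power at d = 0.26 would need 234 per arm.

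**The case against.** The strongest defence has four parts.

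- **The clause is probably misplaced.** The paragraph opens with 140, for which a margin above 10% is correct. This is likely how the error arose, but the sentence as printed ties the margin to 55 per arm, and the margin does not carry over to 115.
- **For the outcome used to size the trial, power is adequate.** This stands. At post-assessment, the time point of the primary group comparison, 79.7% is 0.3 points below target, and the planned adjustment would probably take it well above 80%. The 18-month group comparison is a secondary hypothesis. A reader might infer that the trial is underpowered for expressive language at d = 0.54; the figures do not support that.
- **The 27% is not like for like.** This also stands. The 0.26 is an all-dose estimate set against a 0.54 from medium-to-high-dose studies, the Background says that effects were larger at higher dose, and this trial gives five 60-minute sessions. It would therefore be wrong to present 27% as the trial's receptive power, or to say that no plausible case reaches 80%: an effect of 0.40 with a baseline correlation of 0.7 does.
- **Sizing on one outcome is ordinary practice, and the section says openly that 0.54 is an expressive estimate.** Accepted. The absence of a separate calculation for joint attention is not an error in itself. What is not supported is the unrestricted conclusion that follows.

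**Conclusion.** The concern holds in two limited respects.

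First, the attrition statement is wrong as written. On the plan's own inputs, 55 per arm is a completer count; the final 115 allows 4.3% loss, and the article's own counts already exceed that. The practical loss for expressive language is trivial at post-assessment and about five points of unadjusted power at 18 months, before any gain from baseline adjustment.

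Second, the adequacy claim is not shown for primary language as a whole. Across receptive effects of 0.26 to 0.40, unadjusted power with 109 dyads is about 27% to 54%. With an assumed baseline correlation of 0.5 to 0.7 it is about 34% to 47% at 0.26 and 67% to 83% at 0.40, so only the most favourable combination reaches the target. These ranges rest on near-even splits at follow-up, on assumed receptive effects above 0.26, and on assumed correlations.

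Severity is should-fix. Recruitment has closed, and no analysis or decision rule changes.

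**What to change.** Amend the Sample size section as follows:

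1. State that 55 per arm is the number analysed for 80% power at d = 0.54.
2. Attach the allowance above 10% to the original target of 140 (21%), and say that 115 dyads allow about 4%.
3. Give the unadjusted detectable effects at 80% power: d = 0.54 with 109 dyads and 0.57 with 98, noting that baseline adjustment would improve on these.
4. Limit the adequacy statement to expressive language at d = 0.54.
5. State that receptive language and joint attention were not the basis of the sample size, and give receptive power as a range with the assumed effect sizes and baseline correlations beside it.

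The cost is a few rewritten sentences with less favourable figures. No participants, assessments or analyses are added.
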